**Methods:**

Three-hundred elite athletes from weight-sensitive (ballet, bodybuilding) and less weight-sensitive (soccer, racket sports, basketball) sports will complete assessments at four time points. A subgroup of 90 athletes will participate in clinical interviews. Logistic and hierarchical regressions will identify ED risk indicators and estimate the prevalence of EDs in athletes. Receiver Operating Characteristic (ROC) analyses will assess diagnostic accuracy of single and combined indicators with reporting of sensitivity, specificity, and the Area Under the Curve (AUC). Group differences and measurement invariance of ED instruments will be tested between the athlete group and 300 non-athlete controls.

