### Objectives

The *primary objective* of the study is to evaluate the validity of the model for pathological eating in elite sport [16]. The indicators (weight-sensitivity, weight- and shape pressure, internalisation of a sports discipline-specific body ideal, unhealthy training intentions and behaviour, fatigue) specified in the model are expected to explain variance in ED symptomatology (measured by EAT-26) and/or increase the likelihood of an ED (clinical interviews) in elite athletes. The *second aim* is to investigate whether the diagnostic accuracy of ED identification in elite sports can be improved by combining standardized instruments (e.g., EAT-26) with sport-specific indicators (e.g., ART). The goal is to empirically derive cut-off scores that prioritize high sensitivity to minimize the risk of false negatives, while maintaining acceptable levels of specificity. The *third aim* is to estimate the prevalence of EDs in elite athletes by both the number of diagnosed cases in this cohort and ED instruments. The prevalence in weight-sensitive sports disciplines is hypothesised to be higher compared to less weight-sensitive sport-disciplines and compared to a control group. *Further study objectives* are the identification of protective factors (e.g., sport type, nutrition knowledge) for DE, the investigation of the predictive validity of the indicators, and the association of physiological markers (e.g., body fat percentage) with DE in elite sports. Methodologically, this study aims at investigating whether conventional instruments measure ED symptoms differently in elite athletes than in the control group.

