**Fig. 1 Fig1:**
[figure not shown]
Flow chart of the study. Notes: T0: Baseline assessment, T1-T3: Time points for follow-up assessments, ED: Eating disorder, blinded: Regarding the scores of the index tests

After providing electronic informed consent, participants can access an eligibility screening by following the study link. Based on the eligibility screening, the participants are assigned to either the elite athletes or the control group, or will be excluded from the study (see section participant eligibility and recruitment). After completing the baseline assessment, controls can exit the survey, while elite athletes will be forwarded to an appointment booking system. There, they can optionally schedule an appointment for a clinical interview (online or in person, in German or English) and/or the body measurements approximately one month after baseline assessment. Trained specialists will conduct the clinical interviews and body measurements. Body measurements (i.e., body fat percentage) can also be conducted by an external health care professional chosen by the participant. Interview and body data are documented in an electronic case report file. Links to access the follow-up assessments are send via email by the study staff. All emails and reminders are standardized. Data of each assessment point will be linked using pseudonymized participant codes.

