### Participant eligibility and recruitment

All participants are required to speak and understand English fluently to be included in the study. This study is aimed at elite athletes who (a) practice either ballet, bodybuilding, racket sports, soccer, or basketball, (b) organise their daily life around their sport and (c) regularly participate in competitions or performances [1, 13, 36, 43, 44]. To be assigned to the elite athlete group, the training must have been practiced for at least six months with more than 300 min/week at moderate or higher intensity [36]. Participants, who fulfil the criteria for classification as elite athletes and practice one of the sports disciplines mentioned above, are included in the elite athletes group. Participants who do not meet the criteria of the elite athlete group are assigned to the control group. Participants in the control group may also train regularly but should not match the elite athletes’ criteria. If the participants fulfil the criteria to be considered elite athletes, but do not practice any of the sports disciplines examined in this study, they will be excluded from the study.

Participants are recruited purposefully at sports facilities, sports boarding-houses, ballet academies, ballet companies, sports clubs, fitness fairs, sports events, and on social media. Among other recruitment strategies, we search Instagram accounts affiliated with ball sport-, ballet-, or bodybuilding associations like the International Federation of Bodybuilding and Fitness. Moreover, ballet companies or academies are contacted to inform potential eligible participants about the study and distribute the recruitment material.

A screening prior to baseline assessment enrols eligible participants. They will be asked to provide their contact details in a survey link separate from study data, which is used to contact participants one, six and twelve months after baseline assessment for follow-up assessments (see Table 1.). Participation in the clinical interviews is voluntary for the athlete group.

**Table 1 Tab1:** Assessment Schedule

				Planned assessment time points								
				Athletes					Controls			
Criteria				T0	T1	T2	T3		T0	T1	T2	T3
	*Eating disorder (A) and Disordered eating (B)*											
			Clinical interviews		X							
			Eating Attitudes Test-26	X		X	X		X		X	X
			Eating Disorder Examination Questionnaire		X					X		
			Brief Eating Disorder in Athletes Questionnaire	X	X	X	X		X	X	X	X

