### Outcome measures

The primary outcome is the additional variance explanation in the psychopathology of eating behaviour in the elite sports group by the indicators (∆R²) of our theoretical model of DE [16]. The criteria of the regression models will be measured (A) binary conducting clinical interviews (ED present or absent) and (B) continuous using an ED instrument (severity of ED symptomatology).

*A)* Clinical interviews serve as a reference test. Trained specialists will assess participants for EDs (anorexia nervosa, bulimia nervosa, binge-eating disorder, and others) using ICD-11 criteria [14] in a ~ 30-minute interview. Based on the indicator internalization of a sport-specific body ideal, including muscular body images that can potentially contribute to EDs in elite sports, the criteria for muscle dysmorphia proposed by Pope et al. [45] are also part of the interview. ICD-11 criteria will be evaluated using selected questions of the ED examination interview from Lichtenstein et al. [26], allowing a sports-specific exploration of the fear of weight gain or behaviours to prevent weight gain, weight and shape concerns, food-related loss of control, exercise behaviour, and compensatory behaviours. Additionally, performance enhancing substance use, obsessive healthy eating, and physiological consequences of low energy availability in elite sports like reduced sex drive or menstrual dysfunction are evaluated [26, 46, 47]. In addition to the identification of EDs associated with clinically relevant psychosocial and physical impairments, borderline cases will be documented as DE presentations [48]. In comparison to the ICD-10, the ICD-11 might facilitate diagnosis in men by removing the endocrine disorder criterion [14]. Neither the interviewers nor the participants are informed about the results of the index tests.

*B)* The Eating Attitudes Test 26 [EAT-26; [49] evaluates the frequency of DE behaviours on a 6-point-scale with a cut-off of 12.66 indicating clinical risk in athletes [50, 51]. The EAT-26 is administered at T0, T2 and T3 and is used as a measure of ED symptom severity in the hierarchical regression analyses.

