To identify risk or protective factors affecting DE over time as stated in *further aims*, among others linear-mixed models will be conducted. These models assume that data are missing at random (MAR). Attrition bias will be evaluated by comparing baseline characteristics between participants with complete and incomplete follow-up data. If systematic differences are observed, sensitivity analyses will be considered to assess the robustness of the findings.

Exploratory analysis may include interaction testing, pathway analysis (e.g., structural equation modelling), latent class models, or network analysis to examine complex relationships among predictors and ED symptoms. If systematic differences are observed between athletes participating in the clinical interviews and those participating in surveys only, inverse probability weighting may be applied as a sensitivity analysis to account for potential selection bias by weighting individuals according to their estimated probability of interview participation. If substantial overlap between related constructs is detected, sensitivity analyses using alternative operationalisations (e.g., separate versus composite predictors) will be conducted to evaluate model stability and robustness. Sensitivity– and subgroup analyses may additionally examine models combining clinically diagnosed EDs and subclinical DE presentations. Potential sex differences among athletes in the factor structure of ED instruments will be assessed through a measurement invariance analysis.

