Many studies recruit athletes from various sports disciplines and generalise their results across all elite sports [102], instead of considering sports discipline-specific demands [103]. The focus on distinct sports disciplines permits nuanced analysis of differences in ED psychopathology among those disciplines, and particularly in relation to weight sensitivity, while at the same time reducing generalisability across the broader spectrum of elite sports.

However, methodological challenges remain. Research in elite sports is constrained by a highly selective group with limited availability due to demanding training schedules. This often results in small sample sizes, which reduces statistical power and hinders the detection of small but potentially meaningful effects [104, 105]. To maximize sample size and utilize validated instruments, the online assessments are conducted in English. However, including non-native English speakers may introduce bias due to potential comprehension difficulties and reduce generalisability. To monitor this, participants are asked to report their nationality. Additionally, participant drop-out across the four measurement points is a concern; to mitigate this, reminder notifications will be sent and an expense allowance will be provided. Framing eating behaviour as the primary research focus and the employed recruitment strategies may introduce self-selection bias, attracting athletes who are either currently experiencing DE or are entirely unaffected, thereby limiting the sample’s representativeness. As participants must be informed about the study’s content, this limitation cannot be fully avoided. To mitigate bias, recruitment materials deliberately avoided the term ED and instead referred to eating behaviour, thus better reflecting the study’s broader scope beyond clinical DE. Voluntary participation in clinical interviews improves feasibility but may again attract those with greater symptom burden.

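### Accuracy and diagnosed-case prevalence rest on about 90 self-selected interviewees, and the only correction for that selection is optional and depends on what the data show

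*Protocol article*

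**What the plan says.** The Protocol article's Outcome measures section makes the interview the standard against which instruments are judged: "Clinical interviews serve as a reference test". The Abstract plans 300 athletes in all, and "A subgroup of 90 athletes will participate in clinical interviews". Entry to the interview is the athlete's own choice. After the baseline survey athletes are sent to a booking system: "There, they can optionally schedule an appointment for a clinical interview" (Study design and procedure). Participant eligibility and recruitment repeats it: "Participation in the clinical interviews is voluntary for the athlete group". No random or score-based sampling is described; Sample size calculation aims at about 30 interviews in each of bodybuilding, ballet and ball games.

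Under Planned data analysis, ROC curves, sensitivity, specificity, Youden cut-offs and alternative cut-offs (sensitivity at least 80%, specificity for example at least 70%) are to be calculated for single and combined instruments. Prevalence is to be estimated "by both the number of diagnosed cases in this cohort and ED instruments" (Objectives), and also as the mean model-predicted probability over the athlete sample (Planned data analysis).

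On selection, the Discussion says: "Voluntary participation in clinical interviews improves feasibility but may again attract those with greater symptom burden". The only analysis aimed at it is near the end of Planned data analysis. It applies if systematic differences between interviewees and survey-only athletes are observed, and then "inverse probability weighting may be applied as a sensitivity analysis to account for potential selection bias". What counts as a systematic difference is not stated.

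**The concern.** This is partial verification: the reference result exists for about 30% of athletes, and the athletes decide who they are. If uptake is related to the index-test score, or to symptoms that drive it, the interviewed group holds too many test-positives. Unweighted sensitivity at any given cut-off is then too high and specificity too low. The raw share of diagnosed cases is too high as well.

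The second aim seeks cut-offs that avoid missed cases, so overstated sensitivity is the error in the harmful direction. The article names the risk and its likely direction, and names a suitable method. It then leaves that method to a later decision, taken after the data have been seen and without a criterion.

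**Working it through.** **Inputs from the article.** 300 athletes and 90 interviews, so uptake is 90/300 = 30% (about 30 of 100 in each of three disciplines). Two-sided 5% is used below for significance; the article gives p < 0.05 without stating sidedness. The article gives no figure for differential uptake, so there is none to reproduce.

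**Assumptions.** True sensitivity 0.70, specificity 0.80, ED prevalence 20%; test-positives volunteer *k* times as often as test-negatives.

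**Step 1. True proportions.** TP = 0.20 × 0.70 = 0.14; FN = 0.06; FP = 0.80 × 0.20 = 0.16; TN = 0.64. Test-positive: 0.30.

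**Step 2. Unweighted results among interviewees.** Sensitivity = k·TP/(k·TP + FN); specificity = TN/(TN + k·FP); raw case rate = (k·TP + FN)/(k × 0.30 + 0.70).

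- k = 1.5: 0.21/0.27 = 0.78; 0.64/0.88 = 0.73; 0.27/1.15 = 23%.
- k = 2: 0.28/0.34 = 0.82; 0.64/0.96 = 0.67; 0.34/1.30 = 26%.
- k = 3: 0.42/0.48 = 0.875; 0.64/1.12 = 0.57; 0.48/1.60 = 30%.

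At k = 2 the report would suggest 18 of 100 cases missed, when 30 are.

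**Step 3. Overall discrimination at k = 2.** Youden's J at this cut-off goes from 0.50 to 0.82 + 0.67 − 1 = 0.49. For normally distributed scores with equal variances, the separation is 0.842 + 0.524 = 1.366 SD, so AUC = Φ(1.366/√2) = 0.833. Doubling the weight of scores above the cut-off gives 0.828 by numerical integration. Neither changes much.

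**Step 4. What weighting recovers at k = 2.** Uptake is 0.30/1.30 = 23% in test-negatives and 46% in test-positives; weights are 4.33 and 2.17. The weighted interviewees return 42 true positives, 18 false negatives, 192 true negatives and 48 false positives, which is 0.70, 0.80 and 20%. Effective sample size is 300²/(90 × 2.17 + 210 × 4.33) = about 81 of 90.

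**Step 5. If uptake depends on ED status itself.** Raw case rate = kP/(kP + 1 − P). For k = 2, 20% appears as 0.40/1.20 = 33% and 10% as 0.20/1.10 = 18%; for k = 3, 20% appears as 0.60/1.40 = 43%. Sensitivity and specificity are then unbiased. Weighting on the single score of Step 3 lowers the 33% only to about 29%.

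**Step 6. Would a significance trigger fire?**

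- k = 2: 46% of interviewees test positive against (90 − 41.5)/210 = 23% of the rest. Standard error 0.060, z = 3.84, power about 97%.
- k = 1.5: 39% against 26%. Standard error 0.060, z = 2.18, power about 59%.
- A 0.25 SD difference in a mean score: 0.25/√(1/90 + 1/210) = 1.98, power about 51%.

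**The case against.** The article is open about the problem: it names the bias and the method. An article may leave weighting covariates and the definition of a systematic difference to a fuller document. That stands as regards detail. But the optional and conditional status of the correction is the article's own statement.

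Several stronger readings are tempting and are not supported:

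- *The plan expects symptomatic athletes to volunteer.* The Discussion only says this may happen. Participants are also not told their index-test results, so uptake can follow symptoms but not a known score.
- *The accuracy results as a whole are unsound.* AUC and J barely change at k = 2. The linear EAT-26 regression, one arm of the primary outcome, needs no interview.
- *A weak instrument would pass the plan's target.* At k = 2 apparent sensitivity passes 80%, but apparent specificity of 0.67 fails the example level of 70%.
- *The trigger would usually miss the bias.* At k = 2 it would almost always fire. It is unreliable for smaller imbalances such as k = 1.5, where sensitivity still reads 0.78 for 0.70. Even when it fires, weighting remains optional.
- *All prevalence results are inflated to 33% or 43%.* Those figures concern only the raw case count and assume uptake driven by ED status itself, which baseline weighting removes only in part. The model-based estimate averages over all athletes and so corrects for selection explained by its retained predictors, though for no other selection.
- *Weighted estimates must be the primary analysis.* This is arguable. The evidence supports always reporting them.

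**Conclusion.** The point holds as a cheap improvement; no stated figure is wrong. Sensitivity, specificity, cut-offs and the diagnosed-case rate depend on volunteers, and the article leaves correction of a bias that it names itself to an undefined observation and a later choice. For a true 0.70/0.80 at 20% prevalence, assumed uptake ratios of 1.5 to 3 give apparent sensitivity of 0.78 to 0.875, specificity of 0.73 to 0.57, and a raw case rate of 23% to 30%. The model-based prevalence is partly protected. The uptake ratios, true accuracy and prevalence are all assumptions, so the direction is firmer than the size. The direction itself requires that uptake rise with the score or with symptoms related to it.

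**What to change.** In Planned data analysis, remove the condition that differences must first be observed, and replace the optional wording with a commitment to report weighted sensitivity, specificity, cut-offs and diagnosed prevalence beside the unweighted ones in every case. Prespecify the model of interview participation on T0 data held for all athletes: EAT-26, sex, discipline, age, previous ED diagnosis or treatment, ART and weight pressure. Give bootstrap confidence intervals. State that conclusions about cut-offs and diagnosed prevalence rest on the weighted results where the two differ.

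The cost is low. All variables are already collected and no visits are added. Intervals widen somewhat (effective sample size about 81 of 90 at k = 2). If the sponsor regards this as an important change, the article's own rule calls for informing the ethics committee and updating the registration. Selection on unmeasured factors, including ED status beyond what the T0 variables capture, remains and should be stated as a limitation.

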### Ethics, dissemination, and data protection management

This study has been approved by the Ethics Committee of the University Duisburg-Essen (24-12041-BO). Data collection, storage, and analysis follow the General Data Protection Regulation [98] regulations and the standard operating procedures of the LVR-University Hospital Essen, Germany.

This is a survey-based study supplemented by optional, voluntary clinical interviews and body measurements. No physical or psychological risks are anticipated. Participants receive detailed study information, including data protection, the voluntary nature of the study, and compensation before providing digital informed consent. In case an ED or clinically concerning low body weight are detected, participants will be offered counselling and treatment options through the Clinic for Psychosomatic Medicine and Psychotherapy, LVR-University Hospital Essen, Germany. Study staff is trained in confidentiality and data protection. The study is conducted in accordance with the ethical principles outlined in the Declaration of Helsinki [99]. Pseudonyms link data across assessment points. To protect data while enabling sample size tracking and follow-up assessments, a separate list includes pseudonyms, contact details, participation dates, and group assignments. This list is kept apart from the study data. Results will be shared via peer-reviewed journals, conference presentations, and with relevant stakeholders. Key findings will also be published in lay terms online and promoted through social media.

## Discussion

For the first time, a theoretical model for DE specifically tailored to elite athletes was developed [16]. Building on this theory-based framework, the ENHANCE study aims to empirically examine the model by identifying indicators that can distinguish athletes with and without an ED. This study may not only advance our understanding of EDs in elite sports but may also provide a solid foundation for the development of targeted, evidence-based (preventive) health measures.

The marked inconsistency in prevalence estimates of EDs among elite athletes may be attributable to limited research focus on the topic and to methodological and structural challenges inherent in studies conducted in elite sports [40]. The strengths of the present study address some of these limitations. Its theory-driven approach generates precise hypotheses and specifies relevant indicators for EDs in elite sports. Embedded within a longitudinal design, the theoretical model for ED symptomatology in elite sports supports the interpretation of the results and helps to distinguish between fluctuations and meaningful, theory-based changes [16].

Discrepancies in the results of self-report instruments and clinical interviews [12] suggest underdiagnosis, especially as clinical interviews are rarely applied in elite sports settings [26, 40]. By incorporating clinical interviews as reference tests, this study enhances diagnostic validity and enables more reliable prevalence estimates across weight-sensitive and less weight-sensitive disciplines. The inclusion of a non-athlete control group further allows examination of whether DE manifests differently in athletes.

The limited findings available on EDs in male athletes may be partly due to underdiagnosis likely driven by the use instruments primarily validated in women [20, 40, 51] and a deviation in the expression of ED symptoms [17, 27]. By including a muscular body ideal and using ICD-11 criteria, this study might more reliably diagnose ED in men athletes, helping to overcome stigma and improve support [26, 100, 101].

Many studies recruit athletes from various sports disciplines and generalise their results across all elite sports [102], instead of considering sports discipline-specific demands [103]. The focus on distinct sports disciplines permits nuanced analysis of differences in ED psychopathology among those disciplines, and particularly in relation to weight sensitivity, while at the same time reducing generalisability across the broader spectrum of elite sports.

However, methodological challenges remain. Research in elite sports is constrained by a highly selective group with limited availability due to demanding training schedules. This often results in small sample sizes, which reduces statistical power and hinders the detection of small but potentially meaningful effects [104, 105]. To maximize sample size and utilize validated instruments, the online assessments are conducted in English. However, including non-native English speakers may introduce bias due to potential comprehension difficulties and reduce generalisability. To monitor this, participants are asked to report their nationality. Additionally, participant drop-out across the four measurement points is a concern; to mitigate this, reminder notifications will be sent and an expense allowance will be provided. Framing eating behaviour as the primary research focus and the employed recruitment strategies may introduce self-selection bias, attracting athletes who are either currently experiencing DE or are entirely unaffected, thereby limiting the sample’s representativeness. As participants must be informed about the study’s content, this limitation cannot be fully avoided. To mitigate bias, recruitment materials deliberately avoided the term ED and instead referred to eating behaviour, thus better reflecting the study’s broader scope beyond clinical DE. Voluntary participation in clinical interviews improves feasibility but may again attract those with greater symptom burden.

This study may hold several potential benefits for both research and applied settings in elite sport. By combining clinical interviews with longitudinal assessments, it aims to improve the diagnostic accuracy of ED identification, addressing current limitations in athlete-specific instruments. These insights may inform early, targeted interventions and contribute to the development of evidence-based guidelines for health professionals working in elite sports, with the potential to enhance athlete care and long-term well-being.

